### 13.1.3 Exploratory outcome measures

Other translational research questions will be addressed:

[figure not shown]

- Transcription factor mapping (ChIP-seq) of ER, conducted to assess the progesterin-induced ER reprogramming, as was observed in pre-clinical models [5].
  - ChIP-seq is chromatin immunoprecipitation followed by high throughput DNA sequencing, allowing mapping of the genomic location of transcription factor binding and histone modifications. ChIP-seq will allow demonstration of the robust and predictable ER $\alpha$  binding to novel genomic loci, mediated by PR.
- Change in epithelial mesenchymal transition markers by IHC between baseline and Day 15 (+ $\leq$ 4 Days)
  - To address the question of whether the combination of letrozole and megestrol acetate affects the metastatic potential of ER-positive breast cancer, IHC will be performed to compare the pre- and post-treatment cytoplasmic expression of E-cadherin and N-cadherin.
- Correlate differences in response to treatments with breast cancer genomic profiling datasets
  - To delineate potential underlying germline, somatic and pharmacogenetic reasons for response/non-response to trial treatment. If available, whole genome sequencing data from patients consented and recruited to studies collecting this information may be referenced. We may also aim to correlate our findings within the 4 ER-positive integrative 'clusters' described by the Molecular Taxonomy of Breast Cancer International Consortium [22], based on copy number and gene expression data.

## **14 Statistics**

### **14.1 Statistical methods**

The primary outcome measure is the change in tumour proliferation measured by Ki-67 immuno-histochemical (IHC) assessment (%) at baseline and on day 15 (+  $\leq$ 4 days). The standard t-test will be applied for the primary comparison between Arm A vs Arm (B+C) based on evaluable patients.

The primary analysis for the primary endpoint will be based on the evaluable population (defined as eligible patients who have completed at least 13 [or 80%] of the full 15 Day [+  $\leq$ 4 Days] dosing schedule).

Adverse events will be summarized for the safety population (defined as all patients who have received at least one dose of protocol treatment) using frequency tables and compared using the Wilcoxon Mann-Whitney test or Kruskal Wallis test. All other secondary outcomes will be summarised using the summary statistics and compared between arms using t-test, ANOVA, Wilcoxon Mann-Whitney test or Kruskal Wallis test where ever is appropriate. A comprehensive statistical-analysis plan will be prepared before any analysis is performed.

### **14.2 Number of Subjects to be enrolled**

In this open-label, three-arm, randomized, phase II trial; patients will be randomised in a ratio 1(A):1.5(B):1.5(C) in favour of the 2 combination arms of Letrozole + Megestrol acetate. Our hypothesis is that the addition of Megestrol acetate increases the anti-proliferative effect of Letrozole when given for 2 weeks pre-operatively in patients with early-stage, ER-positive breast cancer, as measured by Ki-67.

Based on the results from the *Opportune* study [23], where a significantly greater geometric mean Ki-67 suppression of 83.8% (one-sided 95% CI,  $\geq$  79.0%) was reported for the combination arm, and 66.0% (95% CI,  $\leq$ 75.4%) for anastrozole alone

[figure not shown]

arm (geometric mean ratio [combination: anastrozole], 0.48; 95% CI,  $\leq 0.72$ ;  $P = .004$ ), this translates to the estimated standard deviation is 0.242. We therefore have assumed a mean 66% reduction in Ki67 for the Letrozole alone arm of PIONEER (Arm A). It is anticipated that there is a mean 77.5% reduction in Ki67 in arms B and C for all patients (approximately one third PR negative, and two thirds PR positive), and a mean 80.0% reduction in Ki67 in arms B and C for patients with PR positive, which was based on the anti-proliferative effect seen in preclinical models [5]. Enrichment design is applied with the overall significance level of 5% (one-sided) ( $5\% (\alpha) = 2.5\% (\alpha_{all}) + 2.5\% (\alpha_{PR+})$ ) and a power of 80%, and common standard deviation of 0.242, using the two-sample t-test comparing Arm A vs. Arm (B+C):

- all patients

a total of 189 patients (Arm A  $n=47$ , Arm B  $n=71$ , Arm C  $n=71$ ) is needed to detect the mean reduction in Ki67 of 66% in Arm A to 77.5% in Arm (B+C);

- patients with PR positive breast cancer

a total of 149 PR positive patients (Arm A  $n=37$ , Arm B  $n=56$ , Arm C  $n=56$ ) is needed to detect the mean reduction in Ki67 of 66% in Arm A to 80.0% in Arm (B+C);

The total number of evaluable patients required is 189 with 149 PR positive. It is anticipated that this will require approximately 10% more patients to be randomised, to account for patients that may not be evaluable.

It is therefore planned to randomise approximately 210 patients with 166 PR positive ( $210 \times 90\% = 189$ ,  $166 \times 90\% = 149$ ).

The comparison of Ki67 reduction between Arm A and Arm (B+C) will be performed for all patients; if  $p_{all} \leq 0.025$ , it can be concluded that the addition of Megestrol acetate increases the anti-proliferative effect of Letrozole for all patients.

If there is no evidence of Ki67 reduction for all patients, the comparison of Ki67 reduction between Arm A and Arm (B+C) will be performed in patients with PR positive only; if  $p_{PR+} \leq 0.025$ , it can be concluded that the addition of Megestrol acetate increases the anti-proliferative effect of Letrozole for patients with PR positive.

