## **8.6 Trial Endpoints**

### **8.6.1 Primary Endpoint**

Change in tumour proliferation measured by Ki67 immuno-histochemical (IHC) assessment (%) between baseline and day 15 (+/-4 Days).

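### The sample size treats geometric-mean Ki67 suppression as an arithmetic mean reduction with SD 0.242, so the stated 80% power is unsupported, though not shown to be too low

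*Protocol*

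**What the plan says.** Section 8.6.1 defines the primary endpoint as "Change in tumour proliferation measured by Ki67 immuno-histochemical (IHC) assessment (%) between baseline and day 15". Section 14.1 fixes the test: "The standard t-test will be applied for the primary comparison between Arm A vs Arm (B+C) based on evaluable patients".

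Section 14.2 rests the planning values on an earlier window trial with a "significantly greater geometric mean Ki-67 suppression of 83.8"% on the combination and 66.0% on anastrozole alone, with one-sided 95% limits of 79.0% and 75.4%. The geometric mean ratio was 0.48, with an upper limit of 0.72. The section says of these results that "this translates to the estimated standard deviation is 0.242", and continues: "We therefore have assumed a mean 66% reduction in Ki67 for the Letrozole alone arm of PIONEER (Arm A").

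The calculation then uses a one-sided 2.5% level for all patients "and a power of 80%, and common standard deviation of 0.242, using the two-sample t-test comparing Arm A vs. Arm (B+C"). It concludes that 189 evaluable patients (47, 71 and 71) "is needed to detect the mean reduction in Ki67 of 66% in Arm A to 77.5% in Arm (B+C"). The PR-positive sample size rests on the same 66% and the same SD. Nothing in the protocol mentions a log transformation or a geometric mean for this trial's own analysis.

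**The concern.** A geometric mean suppression of 66% is a back-transformed mean of log(Day 15/baseline). It is not the arithmetic mean of patients' percentage reductions. Percentage reduction cannot exceed 100% but can be small or negative, so its distribution has a long lower tail. Its arithmetic mean then lies below the geometric-mean figure, and its SD is not the log-scale SD.

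The protocol takes the control mean from one scale, uses it on the other, and attaches an SD whose scale and derivation are not shown. At stake is whether the 80% power for the primary comparison belongs to the test that will be run on the data that will be seen.

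**Working it through.** **1. The plan's own figure.** Inputs from section 14.2: difference 0.775 − 0.66 = 0.115, SD 0.242, one-sided α 0.025, allocation 1:3 for A against B+C.

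- Normal approximation: n(A) = (1 + 1/3)(1.960 + 0.842)² × (0.242/0.115)² = 46.3, so 47, total 188.
- Power with 47 v 142 by the noncentral t: 80.2%.

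The arithmetic is right, provided that 66%, 77.5% and 0.242 are arithmetic quantities on the percentage-reduction scale.

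**2. Is 0.242 a log-scale SD?** Standard errors implied by the one-sided 95% limits, on the log of residual Ki67:

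- anastrozole: ln(0.34/0.246)/1.645 = 0.197
- combination: ln(0.21/0.162)/1.645 = 0.158
- ratio: ln(0.72/0.48)/1.645 = 0.246

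The two arm values combine to √(0.197² + 0.158²) = 0.252, close to 0.246, so the limits behave as log-scale limits. If 0.242 were the per-patient log SD, a 1:1 source trial would have had 4 × (0.242/0.246)² ≈ 4 patients. So 0.242 is not a log SD.

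**3. Where 0.242 could come from.** Read the same limits as if they belonged to arithmetic means. The SEs are 0.094/1.645 = 0.0571 (anastrozole) and 0.048/1.645 = 0.0292 (combination). The pooled SD is √{[(n₁−1)n₁SE₁² + (n₂−1)n₂SE₂²]/(n₁+n₂−2)}. The arm sizes below are assumed, because the protocol gives none:

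- 28 and 28: 0.240
- 53 combination and 27 anastrozole: 0.244

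So 0.242 can be obtained, but only by treating geometric-mean limits as arithmetic ones.

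**4. The same plan on the log scale.** The effect is ln(0.34/0.225) = 0.413. With 47 v 142 and one-sided 0.025, 80% power needs a log SD of at most about 0.87. The source log SD is 0.246/√(1/n₁ + 1/n₂), which depends on the assumed source size:

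| Assumed source size (combination:control) | Log SD | Power at 47 v 142 |
|---|---|---|
| 40 (2:1) | 0.73 | 91-92% |
| 40 (1:1) | 0.78 | 88% |
| 50 (1:1) | 0.87 | 80% |
| 60 (1:1) | 0.95 | 72-73% |
| 75 (2:1) | 1.01 | 68% |
| 100 (1:1) | 1.23 | 51% |

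Where two values appear, they come from the t and the normal calculation. At the sizes in step 3 that explain 0.242, the log SD is 0.92 (28/28) or 1.04 (53/27), with power of about 75% or 65%.

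**5. What the scale does to the means.** If ratios are lognormal with log SD s, the arithmetic mean reduction is 1 − g·exp(s²/2), where g is the geometric mean residual. At s = 0.97 this gives 46% (g = 0.34) and 64% (g = 0.225), not 66% and 77.5%.

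**6. Which test does better.** Simulation of 20,000 trials, 47 v 142, pooled t-test, lognormal ratios without zeros:

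| Log SD | t-test on ratio | t-test on log ratio |
|---|---|---|
| 0.80 | 77-78% | 86-87% |
| 0.875 | 68-69% | 80% |
| 0.97 | 58% | 71% |
| 1.10 | 46-47% | 60-61% |

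Ranges reflect repeat simulations.

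The ordering reverses once zeros occur. Assume a baseline Ki67 of 15%, 1,000 nuclei counted, an offset of half a nucleus, log SD 0.8 and the same zero rate in all arms. With 5% zeros the log test has about 48% power against 74% for the untransformed test. With 10% zeros it is about 32-33% against 68-69%.

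**The case against.** Four points can be made for the plan.

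- **The SD can be recovered.** A reader might infer that the quoted figures cannot produce 0.242. They can, as a pooled SD at ordinary arm sizes (step 3). That stronger claim fails. What stands is that the route crosses scales.
- **Low power is not shown.** A reader might infer that the trial is underpowered. The source sizes are not in the protocol, and the range in step 4 lies on both sides of 80%. If 66%, 77.5% and 0.242 were the true arithmetic values, the planned power would hold.
- **The log test is not free.** A reader might infer that a log-scale test is simply better. That holds for roughly lognormal ratios with few zeros. The protocol gives no distribution, and a modest share of complete suppressions reverses the ordering under a half-nucleus offset.
- **The SAP may settle the scale.** Section 14.1 defers detail to an SAP, and a t-test on a log ratio is still a t-test. The protocol never says that the test is on untransformed values; this is inferred from the endpoint wording and the percentage-point sizing. That relative rather than absolute change is meant can be read from section 14.2 and from the response definition in section 13.1.1.

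The last point does not dispose of the matter. The sample-size basis is fixed in the protocol. An SAP that moved to the log scale would leave 189 resting on an SD that is not a log SD. An SAP that kept percentage reduction would leave it resting on a geometric mean used as an arithmetic one.

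**Conclusion.** The point holds as a fault in the planning inputs. The arithmetic for 189 is correct, but the control mean comes from a log-scale summary and the SD of 0.242 does not belong to that scale. The 80% power is therefore unsupported on either scale, and the documents do not establish that it is lower.

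On the log scale, 80% power is kept if the source log SD is at most about 0.87. By the quoted limit on the ratio, that corresponds to a source trial of no more than about 50 patients at 1:1 or 56 at 2:1. For 40 to 100 patients, power is about 92% to 51%; at sizes that would explain 0.242 it is about 65-75%. All of these sizes are assumptions. The log test's advantage of about 8-15 points at log SD 0.8-1.1 depends on near-lognormal ratios with few zeros.

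**What to change.** Put the effect, the SD and the primary test on one scale, and say which.

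- **Preferred:** analyse log(Day 15 Ki67/baseline Ki67), compare A with B+C on that scale, and report the geometric mean ratio with its interval. Re-derive the power from the source trial's log-scale SD and arm sizes, and restate it if that SD exceeds 0.87. Percentage reduction can stay as a descriptive summary.
- **If percentage reduction is kept for the test:** justify the arithmetic means and the SD from data on that scale, and show how 0.242 was obtained.
- **Either way:** apply the same correction to the PR-positive calculation. For the log analysis, fix the rule for zero counts in advance and check its effect on power by simulation. A half-nucleus offset should not be adopted unchecked.

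The cost is wording in sections 8.6.1, 14.1 and 14.2, matching SAP text, one power calculation and a short simulation. Changing scale does not itself restore 80% power. If the source log SD proves to be above 0.87, the sponsor must either accept a lower stated power or enrol more patients: about 200-224 evaluable patients for a source trial of 60, and 332-376 for one of 100.

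### The 2.5% + 2.5% split is valid but conservative: the nested PR-positive test leaves over a point of the 5% unspent, worth about 5 points of PR-positive power

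*Protocol*

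**What the plan says.** Section 14.2 of the Protocol fixes both the overall level and how it is spent: "Enrichment design is applied with the overall significance level of 5% (one-sided"), written out as the sum of 2.5% for all patients and 2.5% for PR-positive patients. The calculation uses "a power of 80%, and common standard deviation of 0.242, using the two-sample t-test comparing Arm A vs. Arm (B+C").

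Testing is in order. All patients are compared first at 0.025. If that fails, "the comparison of Ki67 reduction between Arm A and Arm (B+C) will be performed in patients with PR positive only", again at 0.025.

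The second group is part of the first: "The total number of evaluable patients required is 189 with 149 PR positive". The same section assumes that about two thirds of the unselected population is PR-positive, and section 14.3 has the share monitored during recruitment. Section 14.2 does not mention the correlation between the two tests.

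**The concern.** Adding 2.5% and 2.5% gives a bound that holds whatever the dependence between the tests. Here the dependence is strong and positive, because most patients in the first test are also in the second. When one test is falsely positive the other often is too, so the chance of at least one false claim is clearly below the sum.

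The sponsor chose to accept a one-sided risk of 5%, but the rule as written uses less. The unspent part could go to the PR-positive comparison, which the enrichment design exists to support. That test would be just short of 80% power at 0.025 if the PR-positive share stayed at two thirds. Section 7.2.1 says the trial is to help decide whether a larger adjuvant trial is worthwhile, so a missed effect has a cost.

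**Working it through.** **Inputs (all from section 14.2).** SD 0.242; difference 0.115 in all patients (66% to 77.5%) and 0.14 in PR-positive patients (66% to 80.0%); allocation 1:1.5:1.5, which is 1:3 for A against B+C; 189 evaluable patients (47 against 142); 149 PR-positive planned, or 126 if the share is two thirds (189 × 2/3).

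**1. The plan's own all-patient figure.** n in Arm A = (1.960 + 0.842)² × 0.242² × (1 + 1/3) / 0.115² = 46.3, so 47, or 188 in total at 1:3. The plan has 47 + 71 + 71 = 189, so it reproduces. The noncentrality is 0.115/0.242 × √(47 × 142/189) = 2.82, and the t-test power at one-sided 0.025 is 80.2%.

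**2. Correlation of the two tests.** With equal SDs and the same arm ratio in both PR groups, ρ = √(n_PR+ / n_all).
- √(149/189) = 0.888
- √(126/189) = 0.816

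**3. Attained familywise error of the stated rule.** With no effect in either population, this is 1 − P(Z₁ < 1.96, Z₂ < 1.96) under a bivariate normal with correlation ρ.
- 149/189: 3.57%. A simulation of the actual t-tests (200,000 runs) gave 3.55%.
- 126/189: 3.85%.

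**4. PR-positive threshold that spends the full 5%.** Keep p_all ≤ 0.025 and solve 1 − P(Z₁ < 1.96, Z₂ < z) = 0.05 for z.
- 149/189: threshold 0.0436
- 126/189: threshold 0.0397

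If only one of the two null hypotheses is true, the error cannot exceed that test's own threshold, so it also stays below 5%.

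**5. Power at these thresholds.** PR-positive power uses the noncentral t with an exact 1:3 split. The noncentralities are 0.14/0.242 × √(37.25 × 111.75/149) = 3.06 and 0.14/0.242 × √(31.5 × 94.5/126) = 2.81. The chance of at least one claim uses the bivariate normal.

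| | 149 PR-positive | 126 PR-positive |
|---|---|---|
| PR-positive power, 0.025 | 85.9% | 79.7% |
| PR-positive power, new threshold | 90.9% | 85.1% |
| At least one claim, 0.025 / 0.025 | 88.7% | 87.2% |
| At least one claim, new threshold | 91.9% | 89.4% |
| All-patient power, either rule | 80.2% | 80.2% |

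With the plan's whole-number split of 37 against 112, the PR-positive figures are 85.8% and 90.7%.

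Separately, the stated inputs need only 128 PR-positive patients for 80% power, not 149. A difference of 0.13 would need 148. If 0.13 was meant (my assumption), PR-positive power at 37 against 112 goes from 80.4% to 86.6%, so the gain does not depend on resolving that.

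**6. Sensitivity to the correlation.** Take the thresholds 0.025 and 0.0436 as fixed and change one assumption at a time.
- Arm A has 31 rather than 37 of the 149 PR-positive patients (my assumption). Then ρ = √[(1/47 + 1/142) / (1/31 + 1/118)] = 0.834 and the error is 5.2%.
- The PR-negative SD is 1.5 times the PR-positive SD (my assumption). Then ρ = 0.789 and the error is 5.4%.

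Recomputing the threshold with the right ρ gives 0.0406 and 0.0385. Both are still well above 0.025.

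**The case against.** The strongest reply is that nothing here is wrong. A significance level is an upper bound, and a rule with 3.6% error does control error at 5%. The split is fixed in advance, applied consistently and easy to explain, and it holds whatever PR-positive share is recruited. The planned power is also met: 80.2% for all patients, and more than 80% for PR-positive patients at the planned 149. All of that stands.

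A reader might infer from the gap between 5% and 3.6% that the design lacks the level it states, or that the trial is underpowered. The documents support neither.

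Two further objections also stand. The 5-point gain belongs to the PR-positive test alone. Under the ordered rule, the chance of any positive claim rises by only 2 to 3 points. Nor is the correlation known exactly from the PR-positive share. PR status is not among the minimisation factors in section 9.3 (grade, subtype, ER intensity), so the arm ratio within PR-positive patients is left to chance, and the common SD is an assumption. Thresholds fixed from the simple formula could let the error drift slightly above 5%. Using the observed counts and variances largely answers this, but error control then rests on a joint normal approximation, which the plain split does not need.

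**Conclusion.** The point holds as an inexpensive improvement to a valid design. The stated rule has a one-sided familywise error of at most about 3.6% (149/189 PR-positive) to 3.9% (two thirds), against the 5% the sponsor chose to spend. Spending the remainder on the PR-positive test adds about 5 points of power there and leaves the all-patient test unchanged. The revised rule makes a claim whenever the present one would.

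The figures rest on the plan's SD and effect sizes, equal SDs in the two PR groups, a 1:3 arm ratio within PR-positive patients, and approximate joint normality of the two statistics. Different counts or SDs move the threshold, but in the cases checked it stays between about 0.038 and 0.044.

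**What to change.** Keep the test order and p_all ≤ 0.025. State in section 14.2, with the detail in the SAP, that the PR-positive threshold will be set so that the total one-sided error is 5% under the bivariate normal distribution of the two statistics. Fix the formula now and evaluate it once the evaluable set is final, before Ki67 results are compared by arm.

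Compute the correlation from the observed arm-by-PR-status counts. With A and B patients per group overall and a and b among PR-positive patients, ρ = √[(1/A + 1/B) / (1/a + 1/b)] when the SDs are equal. If the variances in the two PR groups differ, include them, estimated with arms pooled. Do not rely on √(n_PR+ / n_all) alone. Expect a threshold near 0.044 at 149/189 or 0.040 at 126/189.

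The cost is one calculation and a change of wording, with no extra patients. The downside is that error control then depends on the normal approximation and on a correct correlation, and the rule is harder to explain. If the sponsor prefers the plain split, section 14.2 should describe 5% as an upper bound, with an attained level of about 3.6% to 3.9%.

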### **14.3 Enriched data monitoring**

The patient population will be monitored (PR positive vs. PR negative) regularly during patient recruitment in order to achieve the required sample size for patients with PR positive. This will be regularly reviewed by the Independent Data Monitoring Committee (IDMC) and the recruitment plan will be amended accordingly if needed.

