### **14.4 Criteria for the premature termination of the trial**

Patient recruitment will continue until the target of 189 evaluable patients has been reached.

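### The PR-positive sample size of 149 in section 14.2 does not follow from its stated inputs, which need about 128; 149 gives about 86% power, not 80%

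*Protocol*

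**What the plan says.** Protocol section 14.2 plans a comparison of Arm A with Arms B and C pooled, by two-sample t-test, in all patients and in PR-positive patients. An overall one-sided 5% is split into 2.5% for each. Allocation is 1:1.5:1.5. Both calculations share "a power of 80%, and common standard deviation of 0.242".

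- **All patients:** 66% against 77.5% mean Ki67 reduction, 189 patients (47/71/71). The 77.5% is described as applying to a population that is "approximately one third PR negative, and two thirds PR positive".
- **PR positive:** 66% in Arm A against "a mean 80.0% reduction in Ki67 in arms B and C for patients with PR positive", 149 patients (37/56/56).

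The section concludes: "The total number of evaluable patients required is 189 with 149 PR positive". After allowing 10% for non-evaluable patients, it plans about 210 randomised, 166 of them PR positive.

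Section 14.3 acts on the PR-positive figure: "The patient population will be monitored (PR positive vs. PR negative) regularly during patient recruitment in order to achieve the required sample size" for that group, with IDMC review and amendment of the recruitment plan if needed. Section 14.4 gives the end of recruitment without mentioning PR status: "Patient recruitment will continue until the target of 189 evaluable patients has been reached".

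**The concern.** The two sample sizes differ only in the assumed effect, so each should follow from the same formula. A difference of 14 percentage points instead of 11.5 should shrink the required number by the factor (0.115/0.140)² = 0.675, that is from 189 to about 128. The protocol prints 149.

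This matters because the PR-positive comparison is one of the two tests on which the trial can claim success, and because 149 and 166 are live recruitment targets. If the number is wrong, recruitment is being monitored against a target larger than the stated design requires. If the 80.0% is wrong, the protocol overstates the effect it is sized to detect. A reader cannot tell which.

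**Working it through.** **Inputs (Protocol 14.2):** SD σ = 0.242; one-sided α = 0.025 per population; power 0.80; ratio r = 3 for B+C to A (1.5 + 1.5 to 1); differences δ = 0.775 − 0.66 = 0.115 (all) and 0.80 − 0.66 = 0.140 (PR positive).

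**Formulas.** Normal approximation for Arm A: n_A = (1 + 1/r)(z₀.₉₇₅ + z₀.₈₀)² σ²/δ², with (1.960 + 0.842)² = 7.849. Power is then checked exactly with the noncentral t distribution on n_A + n_BC − 2 degrees of freedom, with noncentrality δ / (σ√(1/n_A + 1/n_BC)).

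**1. All patients, as a control.** n_A = 1.3333 × 7.849 × 0.0586 / 0.01323 = 46.3, rounded up to 47, so 188 in whole 1:3 units. Exact power at the stated 47 against 142 is 80.2%. The protocol's 189 reproduces, which confirms the method and inputs.

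**2. PR positive, same method.** n_A = 1.3333 × 7.849 × 0.0586 / 0.0196 = 31.3, rounded up to 32, so 128 (32/48/48).

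| PR-positive n (A vs B+C) | PR-positive reduction | Exact power |
|---|---|---|
| 149 (37 vs 112), as stated | 80.0% | 85.8% |
| 128 (32 vs 96) | 80.0% | 80.3% |
| 126 (32 vs 94) | 80.0% | 80.1% |
| 149 (37 vs 112) | 79.0% | 80.4% |
| 128 (32 vs 96) | 79.0% | 74.3% |

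The stated 149 exceeds 128 by 21 patients.

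**3. What would give 149?** With 37 against 112, 80% power corresponds to a difference of 0.129, close to the 0.13 of a 79.0% alternative. It also corresponds to an SD of about 0.262, or the number fits roughly 85% power at 80.0% (148). A two-sided 2.5% level gives 152 by the normal approximation and 156 by the t-test, but it would make the all-patient number 228. No single setting of alpha, sidedness and power that was tried gives both 189 and 149.

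**4. PR mix.** 149/189 = 78.8% and 166/210 = 79.0%. Two thirds of 189 is 126; two thirds of 210 is 140. With 77.5% overall and 80.0% in PR positive at a two-thirds mix, the implied PR-negative reduction is 3 × 77.5 − 2 × 80.0 = 72.5%. At 149 PR positive and 40 PR negative, the all-patient mean becomes (149 × 80.0 + 40 × 72.5)/189 = 78.4%, not 77.5%.

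**The case against.** The strongest reply is that the slip is harmless. It gives the PR-positive test more power than claimed. The figure that sets the trial's size, 189, is right, and type I error and the analysis are untouched. That stands, and it limits the weight of the point. It does not make the printed statement correct.

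Three stronger readings are tempting, and the documents do not support them.

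- **That 149 contradicts the two-thirds mix.** Section 14.2 declares an enrichment design and 14.3 provides for PR monitoring, so a recruited share of 79% may be deliberate. What remains is that the 77.5% effect is not restated for that share. At 79% the effect would be slightly larger, so this too errs on the safe side.
- **That PR-negative patients will be turned away, or that 149 will almost surely be missed.** No eligibility criterion or monitoring rule excludes PR-negative patients. The chance of at least 149 PR positive among 189 is 0.0002 at exactly two thirds, but 0.004 at 70% and 0.13 at 75%, all without enrichment. The protocol says approximately two thirds and allows the recruitment plan to be amended.
- **That the PR target is unnecessary and the monitoring can go.** At a two-thirds mix, 189 patients include 128 or more PR positive with probability only 0.41, so without monitoring even the smaller target would be missed 59% of the time. And if 79.0% was the intended effect, cutting to 128 would leave about 74% power.

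Section 14.4 can also be read together with 14.2, where the target is 189 including 149 PR positive. It is loosely worded rather than a competing rule.

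**Conclusion.** The point holds as an error in a stated sample size. On the protocol's own inputs, the PR-positive requirement is about 128, and 149 carries about 86% power rather than 80%. The all-patient 189 is correct. The error favours the PR-positive test, so the cost is not lost power. It is a recruitment target, monitored under 14.3, that cannot be derived from the design as written, together with an all-patient effect tied to a different PR mix from the one the target implies.

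This rests on reading the SD, the one-sided 2.5%, the 80% power and the 1:3 pooled allocation as common to both calculations, as 14.2 states, and on 1:3 balance holding within PR-positive patients (PR status is not among the stratification factors in 9.3). The documents do not show whether the number or the effect is the slip; only the sponsor can say.

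**What to change.** In section 14.2, reconcile the PR-positive number, effect and power in one of two ways:

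1. Keep 149 evaluable and 166 randomised, and state about 86% power for 80.0%. If 79.0% was the intended alternative, correct the effect instead and keep 80% power.
2. If 80.0% and 80% power are both intended, state about 128 evaluable (32/48/48) and about 142 randomised (128/0.9).

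In the same section, state the intended PR mix. If it is 79%, restate the all-patient effect for that mix (about 78.4% on the present assumptions). If it is two thirds, say how the PR-positive target will be reached, since two thirds of 189 is about 126. Make 14.4 refer to the same PR-positive target as 14.2 and 14.3, and keep the PR monitoring in 14.3.

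The first option changes text only and needs no extra patients. The second also needs no extra patients, but it lowers the sample size of a primary hypothesis, so it is a design amendment that needs sponsor agreement and the review described in 18.4. It should be taken only once the sponsor has confirmed that 80.0% is the intended effect.
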